## Discussion

The present study will implement an intervention program for families with mentally ill parents in regular care at multiple sites in Germany and at one site in Switzerland. In the current trial, the program's effectiveness and cost-effectiveness will be evaluated in a randomized-controlled design with a comprehensive health-economic assessment at baseline, 6, 12, and 18 months after baseline assessment. We hypothesize that the CHIMPs intervention improves children's mental health and health-related quality of life compared to the control condition. An important strength of this study is the use of a randomized controlled trial design with a control group receiving treatment as usual. The study design includes a comprehensive health-economic evaluation.

The low-restrictive inclusion criteria allow patients with a variety of psychiatric disorders to take part in the study. Moreover, not only biological parents, but also adoptive parents, foster parents or step parents will be included. This represents an important opportunity to investigate a sample that is representative for this diverse high-risk population in a standard environment.

The CHIMPs family intervention of the present study involves all family members. This setting of the intervention represents an important strength of the study as existing research proves that addressing parents and children jointly produced larger effects of preventive interventions for children of mentally ill parents compared to interventions addressing parents and children individually (23).

In the CHIMPs study, psychopathology will be assessed by multiple perspectives. Most importantly, children's mental health, the primary outcome, will be assessed by a clinical interview by an external rater blind to the family's group assignment. Moreover, psychopathology of the children will be measured by parents' and children's perspectives using the CBCL and the YSR for children 10 years and older. Overall, a wide range of outcome measures (e.g., mental health, health-related quality of life, coping, social support, family relationships) for children and parents will be assessed from multiple perspectives. As multiple perspectives are estimated to be state-of-the art measuring psychopathology (72, 73) and quality of life (74) in children and adolescents, this assessment presents another clear strength of our study.

The extensive assessment of outcomes will allow for a comprehensive analysis of various risk and protective factors relevant for the interplay between parental mental disorders and children's mental health. This analysis will facilitate the further understanding of transgenerational transmission of mental disorders and the adaptation of existing support programs for families with parental mental health problems. Moreover, this study aims at reducing transgenerational transmission of mental health problems in families with parental mental disorders.

An important implication for practice is that all children participating in the study are screened for mental health problems at the very beginning of study participation. This provides the opportunity for an early identification of children with mental health problems who will subsequently be referred to appropriate offers of assistance. All children and adolescents participating in the intervention or the control group with indication for individual support like e.g., psychiatric treatment or psychotherapy will obtain the corresponding referral.

Difficulties could arise from the multicenter design of this study. The combination of both university and supply clinics could lead to differences in the recruitment process. For this reason, possible center effects will be analyzed and treated accordingly during the statistical analysis.

As a large number of therapists from different therapeutic approaches will lead the CHIMPs program, it could be difficult to perform the intervention in a reliable standardized manner. To ensure adherence to the manual, the process and the methods of each session will be documented and analyzed for compliance with the manual.

Experience from this trial will be used to revise the existing manual. The financing of the intervention in regular care beyond the duration of the study will be discussed with health-insurance representatives as part of the study. An important aim of the study is to not only evaluate the CHIMPs intervention in the participating study centers, but to implement it into regular care throughout Germany.

The support provided to families with mentally ill parents should be comprehensive and integrative and therefore oriented toward all family members as the psychosocial and medical starting points for the affected families are equally complex. If successful, the CHIMPs intervention could be the first program for mentally ill parents and their children to be implemented nationwide into regular practice; this could be an important and future-oriented contribution to the improvement of a family-oriented support system for this particular risk group.

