#### Sample Size and Power Calculation

The primary analysis is based on the intention-to-treat population of all children and adolescents with initial psychiatric diagnosis (addressed in hypothesis 4). In a first step, we calculated the number of children and adolescents to demonstrate the assumed effect in this population. Since the intervention takes place at family level, we determined the total number of children and adolescents and their families to be recruited in a second step.

We assume that 18 months after the baseline assessment 76% of children and adolescents in the intervention group and 90% in the control group still have a psychiatric diagnosis according to K-SADS-PL. Further, we suppose that 25/55/15/5% of the families have 1/2/3/4 children, so that on average a family has 2 children and adolescents. With a power of 80%, a two-sided alpha of 5% and an intracluster correlation of 0.05, we need 116 children and adolescents per group (232 children and adolescents in total) with an initial psychiatric diagnosis in 58 families per group (116 families in total) to detect this difference. We rounded up to 240 children and adolescents in 120 families. Additionally, we expect that 15% of children and adolescents show an initial psychiatric diagnosis according to K-SADS-PL. With this assumption, we have to recruit in total 800 families with 1,600 children and adolescents.

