**Figure 1 F1:**
[figure not shown]
Overview of the CHIMPs study design.

If the family has been referred to the intervention group, the therapist who carries out the CHIMPs program is informed and the start of the intervention is initiated. If the family has been referred to the control group, no further treatment is provided within the CHIMPs study.

At 6 (T2), 12 (T3), and 18 (T4) months after baseline assessment, the families will be contacted again by the research staff. The questionnaires and diagnostic interviews for all three follow-up assessments are the same as at the baseline assessment. Families receive a financial compensation (up to €50) if a follow-up assessment is completed, in order to further promote a complete follow-up.

All study-related information will be stored securely at the study site. All records that contain names or other personal identifiers, such as locator forms and informed consent forms, will be stored separately from study records identified by code number. The coordinating study site will oversee the intra-study data sharing process.

All study outcomes, especially the primary outcome papers, will be published in peer-reviewed journals and presented at scientific conferences. All papers and abstracts must be approved by the coordinating site before submission.

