Data will be analyzed and reported according to the CONSORT statement. Mean and standard deviation will be presented for the continuous variables and absolute and relative frequencies for the categorical variables for the whole sample and separated by treatment groups. Since the relatives of a family are subject to common influences, cluster effects are generally to be expected. Therefore, the inferential statistics will be conducted using mixed models with the family and the relatives as random effects. As further covariates, recruitment center, treatment group, time, and the interaction between the two, as well as baseline variables that are unbalanced between the treatment groups. As further possible covariate, the type of clinic (university clinic vs. supply clinic) will be examined. For this purpose, baseline comparisons will be performed. If significant differences are found, this variable will be included in the model as a further fixed effect. We will use the direct Maximum-Likelihood as the statistical estimation procedure in the intention-to-treat population (ITT), which results in unbiased estimations under the missing-at-random assumption. The ITT analysis will be based on the available clinical data from all randomized families. The primary outcome analysis is the treatment group contrast (CHIMPs vs. TAU) at 18 months after baseline assessment in the ITT population of the children with an initial psychiatric diagnosis according to K-SADS-PL in a mixed logistic regression with the above-mentioned specification. The primary outcome is a psychiatric diagnosis according to K-SADS-PL (yes/no). Only the result of this comparison will be interpreted in a confirmatory manner. Additionally, this analysis will be repeated in the per protocol population. Sensitivity analyses will be performed for the primary outcome analysis with different methods of missing value imputation such as multiple imputation and last observation carried forward (LOCF) to study the robustness of the findings. Odds ratios, their 95% confidence intervals and *p*-values will be reported. The type I error will be set at 5% (two-sided). The secondary outcomes will be examined with appropriate methods in the ITT population in an exploratory manner. As far as possible, these outcomes will be operationalised as difference to baseline. Interim analyses are not planned. Subgroup analysis will be conducted on study sites, children's and adolescents' age and children's and adolescents' gender. A detailed statistical analysis plan will be finalized based on an analysis of a blinded, pooled data set. Statistical analyses will be carried out with SPSS, version 24 or newer (IBM Corp, Armonk, NY, USA) R, version 3.6.3 or newer (R Foundation for Statistical Computing, Vienna, Austria) or SAS, version 9.4 or newer (SAS Institute, Cary, NC, USA).

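### The stated models have no therapist term for the CHIMPs arm; if outcomes vary by therapist, the standard error of the group contrast is somewhat too small, so a partially nested sensitivity analysis is worth adding

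*Protocol article*

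**What the plan says.** The Data Analysis section names the family as the source of clustering: "Since the relatives of a family are subject to common influences, cluster effects are generally to be expected". It therefore prescribes "mixed models with the family and the relatives as random effects". The remaining terms are introduced by "As further covariates, recruitment center, treatment group, time, and the interaction between the two", followed by unbalanced baseline variables and possibly the type of clinic. The single confirmatory analysis is run "in a mixed logistic regression with the above-mentioned specification". No therapist term appears. The sample size section likewise carries one correlation, at family level: "With a power of 80%, a two-sided alpha of 5% and an intracluster correlation of 0.05".

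The Discussion states that "a large number of therapists from different therapeutic approaches will lead the CHIMPs program" and concedes that standardised delivery could be hard to achieve. Its answer is to document sessions and check them against the manual; the intervention section adds training, self-rated checklists, recordings and supervision. In the control arm there is no trial therapist: "If the family has been referred to the control group, no further treatment is provided within the CHIMPs study".

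**The concern.** Families treated by the same therapist may have correlated outcomes. Here that correlation can arise in one arm only, so it adds to the variance of the CHIMPs estimate and not to that of the control estimate. A family random effect captures similarity between siblings, not between different families of one therapist. A centre term common to both arms removes differences between centres, not between therapists within a centre.

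The Discussion treats the parallel problem of centre differences as a matter for the statistical analysis, but treats therapist differences as a matter of adherence only. Adherence measures may shrink therapist variation; they do not carry what remains into the standard error. At stake are the width of the confidence interval and the level of the test. Knowledge of how far results depend on the therapist is also at stake, which matters for a programme meant for nationwide roll-out.

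**Working it through.** **1. Does the plan's sample size contain a hidden therapist allowance?** Inputs from the sample size section: 76% against 90%, two-sided 5%, power 80%, family ICC 0.05, mean of 2 children per family.

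- Unpooled two-proportion formula: n = (1.960 + 0.842)² × (0.76 × 0.24 + 0.90 × 0.10) / 0.14² = 109.1 per group.
- Family design effect: 1 + (2 − 1) × 0.05 = 1.05, giving 114.5. With the stated spread of family sizes (coefficient of variation 0.387) it is 1.065, giving 116.2.
- Pooled version: 112 × 1.05 = 117.6.

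The stated 116 per group is reproduced by family clustering alone, so there is no therapist allowance.

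**2. Do CHIMPs families share therapists?** The plan does not say so. 800 families randomised 1:1 give about 400 in CHIMPs. Without sharing, about 400 trained therapists would be needed at seven sites, so sharing is a safe inference for the whole sample.

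**3. Size.** Assumptions, since the document gives neither figure: 14 to 60 therapists; therapist ICC r = 0.01 to 0.05. With m children per therapist and the siblings' correlation already carried by the family effect:

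- CHIMPs design effect: D = 1.05 + (m − 2) × r. The term is m − 2 because a child's sibling is already covered.
- Control design effect: 1.05.
- Variance ratio under the null: R = (D + 1.05) / 2.10.
- Type I error = 2 × [1 − Φ(1.96 / √R)].

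*Primary set* (240 diagnosed children in 120 families, so 120 children per arm):

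| Therapists | m | r | D | R | Type I error |
|---|---|---|---|---|---|
| 60 | 2.0 | 0.01 to 0.05 | 1.050 | 1.000 | 5.0% |
| 28 | 4.3 | 0.05 | 1.164 | 1.054 | 5.6% |
| 14 | 8.6 | 0.01 | 1.116 | 1.031 | 5.4% |
| 14 | 8.6 | 0.05 | 1.379 | 1.156 | 6.8% |

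*Hypothesis 1* (1,600 children, so 800 per arm):

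| Therapists | m | r | D | R | Type I error |
|---|---|---|---|---|---|
| 60 | 13.3 | 0.01 | 1.163 | 1.054 | 5.6% |
| 60 | 13.3 | 0.05 | 1.617 | 1.270 | 8.2% |
| 14 | 57.1 | 0.01 | 1.601 | 1.263 | 8.1% |
| 14 | 57.1 | 0.05 | 3.807 | 2.313 | 19.7% |

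In the worst primary scenario the true standard error under the null is √1.156 = 1.075 times the one the model assumes. At 60 therapists each has one diagnosed family and nothing changes. These design-effect figures approximate the mixed logistic model on the marginal scale.

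**The case against.** - **It belongs in the statistical analysis plan.** A detailed plan is announced and may add the term. But the article does not leave the random effects open: it lists them and applies the list to the primary model. The point is therefore about a stated specification, not a missing detail.
- **The test may keep its level.** Families are randomised individually. If CHIMPs has no effect on any child, it does not matter who delivers it, and the family-level test is valid. Inflation needs therapist effects that differ and average to zero, and an inference that reaches beyond these therapists. This objection stands, and the conclusion has to be conditional on it.
- **The size is assumed.** This also stands. The more literally the large number of therapists is taken, the fewer diagnosed children each one has and the closer the primary test is to 5%.
- **Hypothesis 1 is exploratory.** Correct: only the primary comparison is to be read as confirmatory.
- **Adherence measures act on the cause.** They may reduce therapist variation, but the Discussion itself doubts that standardisation will be complete.

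A reader might infer that the standard errors are too small as a matter of fact and that the confirmatory test exceeds 5%. The document does not support that: it gives no therapist count, caseload or therapist ICC, and an ICC of zero changes nothing. Nor may the figure of 19.7% be carried over to the trial's main conclusion.

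**Conclusion.** The point holds in conditional form. The stated models cover clustering by family and family members, whereas the design is probably also nested by therapist in one arm. If therapist effects vary and the result is to be generalised to other therapists, the precision of the group contrast is somewhat overstated. The effect on the confirmatory analysis ranges from nil to modest; the larger figures concern exploratory analyses only. All figures rest on the assumed therapist numbers and ICCs, on equal caseloads and on the plan's own figure of two children per family, also among the diagnosed. This is a cheap improvement, not a flaw that threatens the primary conclusion.

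**What to change.** Leave the primary model and the sample size as they are. Add to the Data Analysis section a partially nested sensitivity analysis with a random therapist effect in the CHIMPs arm only, applied to the primary contrast and to the hypothesis 1 models. Report the estimated therapist variance, and the number of therapists and families per therapist.

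The cost is a sentence of text and one extra model for each of these analyses. Therapists already fill in a checklist after every session, so recording who treated which family should need little new data.

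There are two downsides. Intervals become slightly wider: in the worst primary scenario at the planned rates, the standard error grows by a factor of √[(0.1824 × 1.379 + 0.09 × 1.05) / (0.2724 × 1.05)] = 1.10. And the model may not converge in the primary subset, where each therapist would contribute only about 2 to 9 binary outcomes. For a sensitivity analysis that is tolerable, provided the plan says that non-convergence will be reported.

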## Ethics Statement

The studies involving human participants were reviewed and approved by the Hamburg Medical Council as well as by the Ethics Committees of all participating study sites. Written informed consent to participate in this study was provided by the participants' legal guardian/next of kin.
